## Abstract

Childhood undernutrition is a major health burden worldwide that increases childhood morbidity and mortality and causes impairment in infant growth and developmental delays that can persist into adulthood. The first weeks and months after birth are critical to the establishment of healthy growth and development during childhood. The World Health Organization recommends immediate and exclusive breastfeeding (EBF). In infants for whom EBF may not meet nutritional and caloric demands, early, daily, small-volume formula supplementation along with breastfeeding may more effectively avoid underweight wasting and stunting in early infancy than breastfeeding alone. The primary objective of this randomized controlled trial is to evaluate the efficacy of formula for 30 days among low birth weight (LBW) infants <6 hours of age and those not LBW with weights <2600 grams at 4 days of age. We will compare breastfeeding and formula (up to 59 milliliters administered daily) through 30 days of infant age vs recommendations for frequent EBF without supplementation, and test the hypothesis that formula increases weight-for-age z-score at 30 days of infant age. The trial will enroll and randomize 324 mother-infant pairs in Guinea-Bissau and Uganda, and follow them for 6 months for outcomes including growth, intestinal microbiota, breastfeeding duration, infant dietary intake, and adverse events. Conservatively estimating 20% loss to follow up, this sample size provides ≥80% power per weight stratum for intervention group comparison to detect a difference of 0.20 with respect to the outcome of WAZ at day 30. This trial was approved by the University of California, San Francisco Institutional Review Board (19–29405); the Guinea-Bissau National Committee on Ethics in Health (Comite Nacional de Etica na Saude, 075/CNES/INASA/2020); the Higher Degrees, Research and Ethics Committee of Makerere University (871); and the Uganda National Council of Science and Technology (HS1226ES). We plan to disseminate study results in peer-reviewed journals and international conferences.

**Trial registration number:**
NCT04704076.

## Introduction

Infants with growth impairment have greatly increased risk of mortality from sepsis, pneumonia, diarrhea, and other infections as well as delayed development [1, 2]. Long-term effects of infant malnutrition include small stature and low body mass, immune dysfunction and increased risk of infections continuing into adulthood, and cognitive impairment, poor school performance, and reduced adult productivity [3, 4]. The first weeks after birth are critical to the establishment of healthy growth, development, and breastfeeding [5, 6]. The World Health Organization recommends immediate and exclusive breastfeeding (EBF), and summarized in 2008 a set of health conditions affecting the infant or mother that warrant alternative feeding [7, 8]. Intrauterine, postnatal, and when complementary foods are introduced are critical phases of growth during infancy. A particularly vulnerable time for growth is immediately after birth, when infants typically lose 5–9% of their birth weight prior to beginning weight gain [9, 10]. While some weight loss is normal, more pronounced weight loss may increase risk of dehydration and growth impairment. In low- and middle-income countries (LMIC), growth problems frequently begin in early infancy and can be difficult to reverse [6, 11, 12]. Preliminary data suggest that two important early predictors of infant growth impairment in sub-Saharan Africa are low birth weight (LBW) and among those not LBW, weight <2600 grams (g) at 4 days of age (data not yet published).

Optimal nutrition can prevent wasting and stunting [13–15]. EBF is widely recommended and provides optimal nutrition for most infants [8, 16], but some exclusively breastfed infants in LMIC fail to thrive. Providing additional nutrition to breastfeeding during early infancy, particularly to infants who initially fail to thrive, may have the potential to prevent wasting and stunting and improve health outcomes [4, 17]. Formula supports weight gain of at-risk infants in early infancy [9, 18, 19]. Tested in two randomized controlled trials in the United States, early, daily, small-volume formula supplementation supported growth without interfering with overall breastfeeding duration [20, 21]. In LMIC, formula may allow infants at risk of future wasting and stunting to begin weight gain earlier; however, formula use has also been associated with mortality [22–24]. Studies have shown that the impact of formula on infant weight can vary by infant age and by breastfeeding status. While formula use increases infant weight in the neonatal period, exclusive use of formula feeding decreases infant weight in the first 2 months, and then increases infant weight later in infancy [9, 18, 25]. Thus, studies are needed in LMIC to demonstrate the effect of formula feeding on infant growth and assess the frequency of adverse events [23, 24].

## Methods and analysis

### Study design and setting

The primary objective of this study is to evaluate the efficacy of formula for increasing weight-for-age z-score (WAZ) at 30 days of age. We chose WAZ rather than weight-for-length z-score (WLZ) or length-for-age z-score (LAZ) as our primary outcome because of WAZ high measurement accuracy. We will conduct a prospective, randomized controlled trial among LBW infants and those not LBW with weights <2600 grams (g) at 4 days of age to compare breastfeeding combined with formula through 30 days of age vs recommendations for EBF without supplementation (Fig 1). We will test the hypothesis that, compared to EBF, formula increases WAZ at 30 days of age (primary outcome) among high-risk infants. Enrolled mother-infant pairs (dyads) will be followed for 6 months for additional outcomes including growth, intestinal microbiota, breastfeeding duration, infant dietary intake, and adverse events. Secondary and exploratory objectives include: 1) determining the effect of formula on WLZ at 30 days of infant age; 2) determining the effect of formula on WAZ, WLZ and LAZ through 6 months of infant age; 3) measuring the effect of formula on breastfeeding duration through 6 months of infant age; and 4) determining the effect of formula on the abundance of *Bifidobacterium infantis* in the infant intestinal microbiota at 30 days of infant age.

**Fig 1 pone.0263129.g001:**
[figure not shown]
Schedule of enrolment, interventions, and assessments.

Beginning in February 2021 and anticipated to last approximately 12 months, this trial will be conducted at Simão Mendes and Cumura Missionary Hospitals in Bissau, Guinea-Bissau and Kawempe Hospital in Kampala, Uganda. These study settings were selected based on our preliminary qualitative data demonstrating readiness, including high levels of healthcare provider knowledge regarding the benefits of breastfeeding and the importance of avoiding unsafe breast milk substitutes such as cow’s milk [26]. Patients and/or the public were not involved in the design, or conduct, or reporting, or dissemination plans of this research. The study staff will be trained in Good Clinical Practice (GCP) as well as study-specific training according to study role(s).

### Study population

The study population will consist of mothers giving birth in participating hospitals and their singleton infants who weigh 2000-2885g at <6 hours of age. A weight maximum of 2885g was selected for the eligibility criteria because infants with birth weight <2500g will be randomized on the day of birth, whereas infants with birth weight ≥2500g will be weighed again on day 4 and will be randomized only if they weigh <2600g on day 4 and have not lost ≥10% of their birth weight. Thus, any infant weighing >2885g at birth will not be eligible for randomization in the study. Trained study staff will screen interested dyads referred by local clinicians during the birth hospitalization. Dyads will be screened in a sequential manner, as much as possible. Trained study staff will assess each dyad for all eligibility criteria (Table 1). Final eligibility for enrollment on day 0 and then randomization on days 0 or 4 will depend on the medical history and examination, appropriate understanding of the study by the mother, and completion of the written informed consent process (S1 File).

**Table 1 pone.0263129.t001:** Study eligibility criteria, visits, measurements, and endpoints.

**Eligibility criteria**	
Inclusion criteria for screening	• Infant < 6 hours old • Infant birth weight estimated at 1500–3500 grams (g) • Mother ≥ 18 years old • Mother intends to breastfeed • Mother with negative HIV test • Mother lives in study catchment area and anticipates availability for all study visits
Exclusion criteria for screening	• Infant a twin or multiple • Infant with known major congenital anomaly, including orofacial cleft, neural tube defect or congenital heart defect • Infant with World Health Organization (WHO) newborn or respiratory danger sign present, including lethargy or unconsciousness, no spontaneous movement, not feeding well, convulsions, raised temperature > 37.5 degrees Celsius, hyopthermia < 35.5 degrees Celsius, jaundice, very fast breathing ≥ 60 breaths/minute, severe chest indrawing, head nodding, flaring, or grunting • Contraindication to breastfeeding at each site as determined by the site’s national or sub-national health authorities • Mother with psychiatric or psychosocial barrier to study participation • Infant enrolled in another study • Mother has had another infant enrolled in this study • Mother unable or unwilling to complete all aspects of the protocol
Inclusion criteria for enrollment	• Infant < 6 hours of age with screening weight 2000–2885 g • All screening inclusion criteria met
Exclusion criteria for enrollment	• Infant < 6 hours of age with screening weight < 2000 g or > 2885 g • Any screening exclusion criteria met
Inclusion criteria for randomization at day 0	• Enrolled infant < 6 hours of age with screening weight 2000–2499 g • All screening inclusion criteria met
Exclusion criteria for randomization at day 0	• Any screening exclusion criteria met
Inclusion criteria for randomization on calendar day 4	• Enrolled infant with weight < 2600 g • All screening inclusion criteria met
Exclusion criteria for randomization on calaendar day 4	• Enrolled infant with weight loss ≥ 10% screening weight on day 4. • Infant with WHO newborn or respiratory danger sign present, including lethargy or unconsciousness, no spontaneous movement, not feeding well, convulsions, raised temperature > 37.5 degrees Celsius, hyopthermia < 35.5 degrees Celsius, jaundice, very fast breathing ≥ 60 breaths/minute, severe chest indrawing, head nodding, flaring, or grunting • Contraindication to breastfeeding at each site as determined by the site’s national or sub-national health authorities • Mother with psychiatric or psychosocial barrier to study participation • Infant enrolled in another study • Mother has had another infant enrolled in this study • Mother unable or unwilling to complete all aspects of the protocol
**Study visits**	
Day 0	• Informed consent obtained • Mother-infant identification number assigned • Infant and maternal contact information, sociodemographic characteristics, current clinical status, and medical history obtained • Infant weight, length, mid-upper arm circumference (MUAC), head circumference measured • Infant physical examination performed • Infant stool sample collected • Maternal weight, height, and MUAC measured • Randomization completed if eligible for randomization
Day 4	• Infant weight, length, MUAC, head circumference measured • Infant hemoglobin measured • Infant and household dietary survey administered • Infant adverse events recorded • Maternal hemoglobin measured • Randomization completed if not already randomized and eligible for randomization
Day 14	• Infant weight, length, MUAC, head circumference measured • Infant dietary survey administered • Infant adverse events recorded
Day 30	• Infant weight, length, MUAC, head circumference measured • Infant stool sample collected • Infant and household dietary survey administered • Infant adverse events recorded • Maternal breast milk sample collected
Day 60	• Infant weight, length, MUAC, head circumference measured • Infant and household dietary survey administered • Infant adverse events recorded • Milk transfer assessed
Day 180 (study exit)	• Infant weight, length, MUAC, head circumference, skin folds measured • Infant stool sample collected • Infant and household dietary survey administered • Infant adverse events recorded • Maternal weight, height, and MUAC measured
**Study measurements**	
Infant weight	• Two infant weights will be obtained at specified study visits, and if these duplicate weights vary by 10 g or more, an additional 2 infant weights will be obtained. Each weight that varies 10 g or less from another weight will be averaged to determine the infant weight.
Infant length	Two infant length measurements will be obtained at specified study visits, and if these duplicate lengths vary by 0.5 centimeters (cm) or more, an additional 2 infant length measurements will be obtained. Each length measurement that varies 0.5 cm or less from another length measurement will be averaged to determine the infant length.
Infant MUAC	Two infant MUAC measurements will be obtained at specified study visits, and if these duplicate MUAC vary by 0.2 cm or more, an additional 2 infant MUAC measurements will be obtained. Each MUAC measurement that varies 0.2 cm or less from another MUAC measurement will be averaged to determine the infant MUAC.
Infant skinfold thickness	Two infant skinfold thickness measurements will be obtained at the biceps and at the triceps at the specified study visit, and if these duplicate skinfold thickness measurements vary by 0.2 cm or more, an additional 2 infant skinfold thickness measurements will be obtained. Each skinfold thickness measurement that varies 0.2 cm or less from another skinfold thickness measurement will be averaged to determine the infant skinfold thickness.
Maternal weight	Two maternal weights will be obtained at specified study visits, and if these duplicate weights vary by more than 0.5 kilograms (kg), an additional 2 maternal weights will be obtained. Each weight that varies 0.5 kg or less from another weight will be averaged to determine the maternal weight.
Maternal height	Two maternal height measurements will be obtained at specified study visits, and if these duplicate heights vary by more than 0.5 centimeters (cm), an additional 2 maternal height measurements will be obtained. Each height measurement that varies 0.5 cm or less from another height measurement will be averaged to determine the maternal height.
Maternal MUAC	Two maternal MUAC measurements will be obtained at specified study visits, and if these duplicate MUAC vary by more than 0.2 cm, an additional 2 maternal MUAC measurements will be obtained. Each MUAC measurement that varies 0.2 cm or less from another MUAC measurement will be averaged to determine the maternal MUAC.
Adverse event	Any untoward medical occurrence
Serious adverse event	Any untoward medical occurrence that meets any of the following criteria: • Results in death • Is life-threatening • Requires inpatient hospitalization • Results in persistent or significant disability/incapacity • Is important AND, based upon appropriate medical judgment, may jeopardize the health of the enrolled infant or require medical or surgical intervention to prevent one of the outcomes listed above.
**Study endpoints**	
Primary endpoints	• Weight-for-age z-score at 30 days of age
Secondary and exploratory endpoints	• Weight-for-length z-score at 30 days of age • Weight-for-age z-score, weight-for-length z-score, and length-for-age z-score through 6 months of age • Duration of breastfeeding through 6 months of age • Abundance of *Bifidobacterium infantis* in the intestinal microbiota at 30 days of age

### Randomization and study procedures

Following enrollment, trained study staff will perform day 0 study procedures (Table 1) according to the most recently approved version of the protocol (current V.2.1, January 2021). Randomization to intervention group will be stratified by country and by weight at time of randomization (day 0 weight 2000–2249g; day 0 weight 2250–2499g; day 4 weight 2250–2424g; day 4 weight 2425–2599g), with 1:1 randomization within each stratum. If the enrolled infant weighs 2000–2499g on day 0, the dyad will be randomized on day 0. If the enrolled infant weighs 2500-2885g on day 0, the dyad will not be randomized on day 0; no intervention will be given on day 0 and the study team will follow the infant and weigh the infant again on day 4. If the enrolled but not yet randomized infant weighs <2600g on day 4, the dyad will be randomized on day 4; however, if the enrolled but not yet randomized infant weighs ≥2600g or has a weight loss ≥10% of birth weight on day 4, the dyad will exit the study. Random allocation will be accessed through a password-protected secure program (randomize.net) on a study device. While study staff and mothers will not be blinded to intervention assignment, the study staff will have no foreknowledge of intervention assignment. Participants will be enrolled with complete concealment of intervention so that both study staff and participants will learn of intervention allocation upon randomization.

Various mitigation measures will be put in place to reduce the possibility that the study’s conduct will impact the acceptability or distribution of formula within the postpartum ward or healthcare provider counselling and support for breastfeeding. First, all formula will be kept out of sight of patients and healthcare providers in a locked cabinet or locked room unless in active use by study staff or participants. Second, study activities will occur in a private room within in the hospital or in the participant’s home rather than on the postpartum ward. Third, prior to randomization, formula will be stored in an opaque container, so that only mothers who are randomly assigned to the study intervention will see it. Fourth, the study will not advertise for participants and will not distribute any materials to participants other than those required by the respective ethics committees.

For enrolled dyads who are randomized, the intervention will either be 1) breastfeeding combined with Similac Pro-Advance formula consisting of up to 59 milliliters (mL) of individually-prepackaged, single-use liquid, iron-fortified infant formula (Similac, Abbott Nutrition, Columbus, Ohio) administered daily through 30 days of infant age followed by EBF through 6 months of infant age; or 2) frequent EBF without additional food or fluid (including water) through 6 months of infant age (control, current standard of care). According to available product information, the intervention formula contains 64.3 kcal/100 mL with a protein content of 1.33 g/100mL and iron content of 1.2 mg/dL.

For dyads randomly assigned to the formula intervention, trained study staff will instruct the mother to breastfeed the infant on demand and at least 8 times a day, and to supplement the infant daily by offering a single-use 59-mL bottle of formula immediately following a breastfeeding and allowing the infant to consume until the infant discontinues feeding and within one hour of opening. The amount of formula consumed by the infant at each feeding will be recorded by study staff. A single-use sterile nipple will also be provided with each bottle. Trained study staff will directly observe four daily formula feedings and then subsequently will deliver two 59 mL formula bottles and two single-use sterile nipples to mothers every other day until 30 days of age with instructions to continue once daily formula supplementation, saving any formula leftover after the feedings to return to the study team to measure and destroy. For dyads randomly assigned to EBF, trained study staff will provide the mothers the identical breastfeeding advice as the formula group with the exception that no supplementation should be given. Medical management of participants will be provided by their usual healthcare providers, not by study staff.

On days 4, 14, 30, 60 and 180, enrolled and randomized dyads will be assessed by trained study staff (Table 1). Infant (naked) weight will be measured using a Seca 334 scale (Seca Inc., Wandsbek, Germany) calibrated before each use. Infant length will be measured using a Seca 416 infant stadiometer and infant mid-upper arm circumference (MUAC) measurement using infant MUAC tape. When measuring infant skinfold thickness, standard skinfold calipers will be used. Maternal weight, height, and MUAC will be measured using standard scales, stadiometers, and MUAC tape, respectively. Infant and maternal hemoglobin will be measured by Hemocue at the day 4 study visit and infant stool samples collected for future intestinal microbiota analysis at the days 0, 30 and 180 study visits. An infant dietary survey (S1 File) will be administered at each scheduled study visit. All infants will be monitored at each study visit for signs or symptoms of illness (fever, low body temperature, blood in stool, profuse/watery diarrhea, vomiting, difficulty breathing, lethargy/decreased consciousness, convulsions, jaundice, and umbilical redness) or any growth problems or adverse events, including serious adverse events. If infant death is ascertained at any follow-up study visit, trained study staff will administer the relevant WHO verbal autopsy instrument.

Maternal milk samples will be obtained from consenting enrolled mothers on the day 30 study visit immediately following breastfeeding, with mothers asked to hand express 10 mL breast milk from each breast for a total of 20 ml. These breast milk samples will be frozen for future analysis. An infant breast milk volume measurement at 2 months is planned in a subsample of 60 mothers, 30 infants at each study site, by specially trained study staff using the deuterium oxide dose-to-the-mother method, which involves mothers consuming a small volume of deuterium oxide diluted in a beverage and collecting subsequent maternal and infant urine samples over a series of days.

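### Length is hand-read by study staff who know the arm, so the secondary LAZ and WLZ endpoints are open to expectation bias that the duplicate rule does not control; the primary WAZ is little exposed

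*Protocol article*

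**What the plan says.** All of this is in the protocol article.

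- **Blinding.** Randomization and study procedures states: "While study staff and mothers will not be blinded to intervention assignment". The protection described is concealment up to the moment of randomisation. Nothing is said about masking afterwards.
- **Who measures.** The same section states: "On days 4, 14, 30, 60 and 180, enrolled and randomized dyads will be assessed by trained study staff".
- **Who supports feeding.** The same term is used for the intervention: "Trained study staff will directly observe four daily formula feedings and then subsequently will deliver two 59 mL formula bottles".
- **Instruments.** For weight: "Infant (naked) weight will be measured using a Seca 334 scale (Seca Inc., Wandsbek, Germany) calibrated before each use". Length is taken on an infant stadiometer.
- **Repeat rule.** Table 1 (Study measurements) asks for two lengths, and "if these duplicate lengths vary by 0.5 centimeters (cm) or more, an additional 2 infant length measurements will be obtained". The trigger for weight is 10 g.
- **Endpoints.** WAZ at day 30 is the only primary endpoint. Study design and setting says it was preferred to WLZ and LAZ for its measurement accuracy. Outcomes hypothesises a gain of 0.20 z for WAZ at day 30, for WLZ at day 30, and for WAZ, WLZ and LAZ through 6 months.
- **Acknowledged bias.** Limitations and bias covers non-adherence, loss to follow-up, fuller adverse-event reporting in the formula arm and the effect of extra weight monitoring. It does not mention anthropometric readings taken with knowledge of the arm.

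**The concern.** Mothers and the staff who support feeding cannot practically be masked. That does not oblige the trial to have its outcomes read by people who know the arm, yet the article declares study staff unblinded without exception and gives them all follow-up measurements. The visit itself also reveals the arm: the dietary survey is given at every scheduled visit and EBF counselling is given to the control arm at each visit. No order is set that puts measurement before either.

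Infant length depends on how the child is positioned and where the reader sets the board. A reader who expects one arm to grow better can shift readings slightly and consistently. Such a shift does not average out with more infants. The planned permutation test does not remove it either, because it takes the recorded values as the data.

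Three of the hypotheses stated at 0.20 z rest on length: WLZ at day 30, WLZ through 6 months and LAZ through 6 months. What is at stake is how those secondary and exploratory results can be interpreted.

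**Working it through.** The article gives no figure for reading error between arms, so there is none to reproduce. The calculation asks how large a given shift would be against the article's own 0.20.

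**Inputs from the article:** hypothesised difference 0.20 z; repeat triggers 10 g and 0.5 cm; 324 dyads, 1:1, 20% loss, hence 324 × 0.8 / 2 = 129.6 analysed per arm.

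**Assumed inputs (not in the article):** one WAZ unit is 450–600 g and one LAZ unit 1.9–2.1 cm at day 30; between-arm length shift 0.1–0.25 cm; for WLZ, length about 50 cm, weight proportional to length to the power b = 2.5–3.5, and a coefficient of variation of weight at given length of 8–11%; outcome SD 1.0, varied from 0.8 to 1.2.

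**1. Does the duplicate rule control a shift?** It compares two readings of one infant. If both are 0.2 cm too long, their difference is unchanged, no repeat is triggered and the average is 0.2 cm too long. The rule limits random disagreement and says nothing about how large a systematic shift might be.

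**2. Weight.** Shift in WAZ = grams / grams per unit.
- 10 / 600 = 0.017 and 10 / 450 = 0.022.
- Divided by 0.20: 8–11%.

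**3. Length, LAZ.** Shift in LAZ = cm / cm per unit.
- Smallest: 0.1 / 2.1 = 0.048. Largest: 0.25 / 1.9 = 0.132.
- Divided by 0.20: 24–66%.
- With a wider assumed unit of 1.7–2.5 cm: 0.1 / 2.5 = 0.040 to 0.25 / 1.7 = 0.147, or 20–74%.

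**4. Length, WLZ.** A longer recorded length raises the expected weight, so WLZ falls. Approximate size = (cm / 50) × b / CV.
- 0.1 cm: 0.002 × 2.5 / 0.11 = 0.05 to 0.002 × 3.5 / 0.08 = 0.09.
- 0.25 cm: 0.005 × 2.5 / 0.11 = 0.11 to 0.005 × 3.5 / 0.08 = 0.22.
- The sign is opposite to LAZ.

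**5. Effect on a two-sided 5% test with no true difference.** SE = SD × √(2 / 129.6), which is 0.124 at SD 1.0. Rejection rate = Φ(b/SE − 1.96) + Φ(−b/SE − 1.96), where b is now the bias in z units (normal approximation).

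| Bias (z) | SD 1.0 | SD 0.8 to 1.2 |
|---|---|---|
| 0 | 5.0% | 5.0% |
| 0.05 | 6.9% | 7.9% to 6.3% |
| 0.10 | 12.7% | 17.2% to 10.3% |

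These figures show what a shift of the stated size would do. They are not evidence that one will occur.

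**The case against.** The strongest reply is that the design already protects what matters most. The primary endpoint rests on a scale calibrated before each use with duplicate readings, and the authors kept length indices out of the primary outcome because weight is measured more accurately. That stands, and it confines the point to secondary and exploratory endpoints. A reader might infer from the unblinded staff that the day-30 WAZ result is in doubt; step 2 of the working does not support that.

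A reader might also infer that one person takes both readings of a pair, knowing the arm and the first value. The article does not say so. Table 1 is in the passive and names neither the measurer nor the order of recording. Nor does the shared term for staff prove that the same individuals feed and measure: the article mentions training by role, and such detail may sit in the full protocol or the operating procedures. The point needs neither inference, because all study staff are declared unblinded.

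The size is assumed, and the 0.5 cm trigger lends it no support, since it concerns disagreement within a pair. The LAZ unit is a day-30 figure, while LAZ is followed to 6 months. Both objections stand, which is why the figures are illustrative only.

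Finally, a reader might picture a bias favouring formula on every growth endpoint. One length shift moves LAZ and WLZ in opposite directions, so it cannot. It could still create a false gain in one while masking a true gain in the other.

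The pragmatic design, standardised training and data audits are fair points too, but none of them masks the arm or detects a consistent shift.

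**Conclusion.** The concern holds for the length-based endpoints. The article states that study staff are unblinded and assigns them every follow-up measurement, so this is a stated design choice and not a detail lost in condensation. The duplicate rule does not control a shift common to both readings, and the limitations section does not acknowledge the risk.

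Under the assumed 1.9–2.1 cm per LAZ unit, a between-arm shift of 0.1–0.25 cm would amount to 0.05–0.13 LAZ, or 24–66% of the hypothesised 0.20, with the opposite sign in WLZ. That the risk exists follows from the text; its size rests on an assumed shift and an assumed unit. The primary WAZ is little exposed, at about 0.02 z for 10 g. The point does not affect the sample size or the primary conclusion, and is worth acting on because the remedy is cheap.

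**What to change.** Amend Randomization and study procedures as follows, from day 14 onward:

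1. Take weight and length first at each visit, before the dietary survey, any counselling and any formula delivery.
2. Where the roster allows, have them taken by an existing trained staff member who does not deliver formula to that dyad.
3. Hide the arm and the values from previous visits on the data form until the readings are entered. Earlier weights are then still available for the existing safety checks. Use the same layout for the paper fallback forms.

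Add a sentence to Limitations and bias saying that the length endpoints may carry residual reading bias, and that one such shift would act in opposite directions on LAZ and WLZ.

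Locking the first reading of a pair before the second is taken would not be enough, because it leaves a shift common to both untouched.

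The cost is a form setting, a visit-order rule and some scheduling burden, felt most at small sites. No new post and no change in sample size is needed. Masking will be incomplete, because mothers or the home setting may reveal the arm, so the change reduces the exposure without removing it.
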